### Secondary Outcomes

Secondary outcomes (eg, 3XF8W step count, 10-meter walk, and PLUS-M subscales) will be analyzed using paired *t* tests or Wilcoxon tests at α=.05. Carryover effects will be assessed and, if present, accounted for in sensitivity analyses. As no multiple comparison corrections will be used for secondary analyses, resulting in a higher familywise type I error rate, all secondary results will be considered exploratory and hypothesis generating rather than confirmatory.

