**Figure 1. F1:**
[figure not shown]
META Arc (WillowWood).

In our previous study, 21 participants with unilateral below-knee amputation had 16 models of usual prosthetic feet, making comparisons between the usual foot and an investigational foot challenging [4]. Also, comparisons with the usual foot do not isolate the benefits of the unique features of the investigational foot. In the previous study, a locking feature eliminated the mediolateral motion, rendering the foot comparable to a typical energy storage and return foot. This was only completed for gait testing protocols in the laboratory; participants stated they had no opportunity for community testing of the locked version. The current study attempts to overcome some of these limitations.

This paper outlines the procedural approach for a randomized clinical trial designed to evaluate the impact of a novel frontal plane ankle technology on individuals with above-knee or bilateral amputations or those with below-knee amputations classified at an MFCL K2. By using a double crossover design and focusing on person-centered outcomes, this study seeks to improve our understanding of how advanced prosthetic feet can enhance functional mobility, balance, and daily activity participation for individuals with complex amputation profiles. A two-period or double crossover research design provides more data per participant, balances potential carryover effects, and improves statistical power and precision by having each participant’s response with the usual prosthetic foot, with the novel foot in both the locked and unlocked position, and with the usual prosthetic again. The mixed methods approach used in this study, which incorporates qualitative insights from interviews, daily experiences recorded in logbooks, and surveys, along with objective measures from standard functional tests, provides a comprehensive evaluation of the novel prosthetic foot. This protocol paper can be a model for not only evaluating prosthetic components but other assistive technologies as well.

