### Procedures

#### Randomization

Stratified by study site, block randomization will be used to determine the order in which participants receive the locked and unlocked investigational prosthesis. Randomization will be completed and maintained through Research Electronic Data Capture (REDCap), a secure, Health Insurance Portability and Accountability Act–compliant web application for building and managing online surveys and databases.

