##### B2 (Second Intervention Phase)

The frontal plane linkage is adjusted to the alternate configuration (locked or unlocked), and participants continue regular use of the study prosthesis for another two weeks. Data collection procedures mirror those in B1. This phase concludes with standardized assessments and a semistructured interview to compare experiences with both foot configurations.

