### Statistical Analysis

The primary analysis will compare the META Arc foot in locked versus unlocked configurations. Statisticians will remain blinded to condition labels, analyzing outcomes as Condition X versus Y, with knowledge of the order (X→Y or Y→X), but not which corresponds to locked or unlocked.

Descriptive statistics (means and SDs for continuous variables; counts and percentages for categorical variables) will be used to summarize participant characteristics, stratified by amputation group. All analyses will be performed separately for each group.

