### Power

With n=30 for the above-knee and K2 groups, the study is powered (>80%) to detect a standardized effect size of 0.53. In the bilateral group (n=16), the power is greater than 50% for the same effect size. Preliminary data show larger effects (eg, 0.98 for the 3XF8W), supporting adequate power. Although underpowered to detect a meaningful difference in the bilateral group, 16 subjects is in line with other gait studies that have published data on 10 [13], 15 [14], or 19 [15] subjects with bilateral amputations, a challenging population to recruit and enroll. The study is also powered (81%) to detect a 75% preference for one configuration (vs 50% under the null) using a sign test with n=30. Although no minimal clinically important difference has been established, it is predicted that a standardized effect of at least 0.50 will correspond to an impactful improvement in participants’ physical function.

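### The design does not balance carryover as the Introduction claims, and the carryover sensitivity analysis runs only if a check with very low power finds something

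*Protocol article*

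**What the plan says.** The Introduction of the protocol article describes the design's advantages: "A two-period or double crossover research design provides more data per participant, balances potential carryover effects", along with better power and precision.

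Under Randomization: "Stratified by study site, block randomization will be used to determine the order in which participants receive the locked and unlocked investigational prosthesis". There are thus two sequences, locked then unlocked and the reverse. Each configuration is used once. The A periods on either side use the participant's usual foot and repeat neither configuration.

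The B2 (Second Intervention Phase) section describes the switch: "The frontal plane linkage is adjusted to the alternate configuration (locked or unlocked), and participants continue regular use of the study prosthesis". No washout is described. Assessment comes at the end of the phase, after two weeks in the new configuration.

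Under Statistical Analysis: "All analyses will be performed separately for each group". Under Secondary Outcomes: "Carryover effects will be assessed and, if present, accounted for in sensitivity analyses". The Primary Outcomes section, which sets out the MANOVA and the paired tests, mentions neither carryover, period nor sequence.

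The Discussion lists as a limitation that participants may go on getting used to the foot in the following period, and that this could bias the results.

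**The concern.** Two statements are at issue.

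The first is the claim of balance. In a two-period, two-sequence comparison, randomizing the order removes a carryover that is the same from either configuration. It does not remove one that differs, such as movement habits learned with the foot unlocked that persist after locking. Differential carryover is aliased with sequence and with treatment-by-period interaction, and it goes straight into the locked-versus-unlocked estimate. The Introduction's claim does not fit with the limitation in the Discussion.

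The second is the words *if present*. They make the sensitivity analysis depend on detecting carryover. With analyses done separately in groups of 30, 30 and 16, that detection rests on roughly 15 against 15 people, or 8 against 8. If the check rarely succeeds when carryover exists, the sensitivity analysis will usually be skipped when it is needed.

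At stake is what the trial can conclude about its primary contrast, including the possibility that a real benefit of the unlocked foot is diluted and missed.

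**Working it through.** **Inputs.** From the Power section: "With n=30 for the above-knee and K2 groups, the study is powered (>80%) to detect a standardized effect size of 0.53"; and n=16 with power above 50% for the same effect in the bilateral group. From Primary Outcomes: α=.05. Assumed, because the article does not give them: two-sided testing; equal sequence sizes (15/15 and 8/8); 0.53 expressed in SDs of the paired difference; a common within-person correlation ρ across A1, B1 and B2, varied over .5 to .9 with ρ=0 as an extreme; and a differential carryover equal to a fraction f of the treatment effect.

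**Step 1: the plan's own figure.** For a paired t test with noncentrality 0.53√n, power is 80.1% at n=30 and 51.0% at n=16. Both stated figures reproduce, which supports reading 0.53 as mean difference over SD of differences.

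**Step 2: bias.** Let δ be the unlocked-minus-locked effect, c_U and c_L the carryover from unlocked and from locked, and π the period effect. The expected unlocked-minus-locked difference is:
- locked first: δ + c_L + π
- unlocked first: δ − c_U − π

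With equal sequences the average is δ − λ/2, where λ = c_U − c_L. If c_U = c_L, carryover cancels. If not, half of the difference remains. With unequal sequences even an equal carryover leaves a residue in the plain paired difference, as a period effect does: an 18/12 split leaves (18−12)/30 = 20% of it. Randomization is stratified by site and not by amputation group, so equality within a group is not assured.

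**Step 3: power to detect λ.** Differential carryover shows up as a difference between sequences in the sum B1+B2. With unit variance:
- λ = f × 0.53 × √(2(1−ρ))
- SD of the sum = √(2(1+ρ)), so the unadjusted standardized difference is f × 0.53 × √((1−ρ)/(1+ρ))
- residual SD given A1 = √(2(1−ρ)(1+2ρ)), so the A1-adjusted standardized difference is f × 0.53 / √(1+2ρ)

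Noncentral t with n/2 per sequence (n−2 degrees of freedom, or n−3 after adjustment), two-sided .05, f=1:

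| ρ | n=30, unadjusted | n=30, A1-adjusted | n=16, unadjusted | n=16, A1-adjusted |
|---|---|---|---|---|
| 0 | 28.9% | 28.8% | 16.7% | 16.6% |
| .5 | 12.8% | 16.8% | 8.8% | 10.7% |
| .7 | 9.1% | 14.8% | 7.0% | 9.7% |
| .8 | 7.5% | 14.0% | 6.3% | 9.4% |
| .9 | 6.2% | 13.3% | 5.6% | 9.0% |

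With f=0.5 and ρ .5 to .9, unadjusted power is 6.9% to 5.3% at n=30 and 5.9% to 5.1% at n=16. Testing at .10 with f=1 raises the unadjusted range only to 21.1%–11.8% at n=30 and 15.7%–10.9% at n=16.

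**Step 4: cost to the primary contrast.** When carryover acts in the diluting direction, the effective size is 0.53 × (1 − f/2). For f=0.5 this is 0.53 × 0.75 = 0.3975, and paired power falls from 80% to 56% at n=30 and from 51% to 32% at n=16. For f=1 the shift is 0.53/2 ≈ 0.27 SD of the paired difference.

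**Step 5: what a first-period comparison can show.** B1 compared between sequences and adjusted for A1 has residual SD √(1−ρ²), so the standardized effect is 0.53 × √(2/(1+ρ)), that is 0.61 to 0.54 for ρ .5 to .9. Power is 37% to 30% at n=30 and 21% to 17% at n=16.

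**The case against.** The article names no test, significance level or decision rule for carryover, and such detail normally belongs in an analysis plan that is not shown here. That stands: the absence of a named method is not the point, and the power figures describe the checks this design allows, not a procedure the article prescribes. They depend on assumed correlations and on a carryover as large as the full effect.

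Participants also spend two weeks in the new configuration before assessment. This reduces carryover but does not exclude it, as the Discussion accepts. Nothing in the article shows that carryover will in fact occur or how large it would be.

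Three stronger readings are tempting and not supported:
- A reader might infer a two-stage procedure in which a carryover pretest selects the primary analysis. The article confines the consequence to sensitivity analyses, and the primary MANOVA does not depend on it.
- A reader might infer that the contrast will be reported as free of carryover. No section says so, and the Discussion discloses possible bias.
- A reader might infer from its place under Secondary Outcomes that the provision excludes the primary outcomes. The sentence is general, and a heading in a condensed article is too little to carry that conclusion.

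Finally, the first-period comparison is itself imprecise: at n=30 its 95% interval is about ±0.65 to ±0.73 SD of the paired difference (ρ .5 to .9), too wide to reveal a shift of 0.27. That is true, and it limits how the result should be read. It does not justify making its appearance conditional on a check that is weaker still.

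**Conclusion.** The point holds in two parts. The Introduction's claim that the design balances carryover is wrong as written: only equal carryover cancels, and only with equal sequence numbers. It also does not fit with the limitation conceded in the Discussion. The conditional sensitivity analysis is a weak safeguard. Even for a differential carryover as large as the effect the trial is sized for, a check at .05 would detect it about 6–17% of the time at n=30 and 6–11% at n=16 for ρ from .5 to .9, with or without A1 adjustment, and only about 29% of the time at n=30 if ρ were 0. A result of no carryover would therefore say little about the primary contrast. These figures rest on the assumptions listed above, and the size of any real carryover is unknown.

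**What to change.** - Delete the *if present* condition. Keep the crossover comparison as the primary analysis.
- For the TUG, the 3XF8W and the Four Square Step Test, always report within each amputation group a B1-only comparison between sequences, adjusted by ANCOVA for the A1 value, beside the crossover estimate. State in advance that it is read for direction and size, not for significance.
- Replace the Introduction's claim of balance with a statement that carryover is assumed equal for the two configurations and that this cannot be reliably verified in this design, in line with the limitation in the Discussion.

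The cost is wording and one extra, imprecise table. The A1 and B1 assessments are already collected, so no new data, visits or change to the primary test are needed.

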### Logbook and Walkway Data

Logbook variables (eg, perceived support on challenging surfaces) will be compared using paired *t* tests or Wilcoxon tests. Fall counts will be analyzed with a sign test. Gait variables (eg, step width, double support time) from the Zeno walkway will be analyzed descriptively.

### Qualitative Analysis

Interviews will be transcribed via Microsoft Teams or Zoom (Zoom Communications Inc) and analyzed using an inductive thematic approach. Open coding will identify themes, followed by focused coding to group codes into broader categories. Multiple codes may apply to individual responses. Qualitative analysis will follow current standards for rigor and reporting.

## Results

This study protocol, funded by the Department of Defense Orthotics and Prosthetics Outcome Program (OP220033), was approved by the University of Washington’s IRB, the University of South Florida’s IRB, and the US Army’s Office of Human Research Oversight in March of 2023. As of September 2025, a total of 66 subjects have completed the study, including 17 with below-the-knee prostheses, 34 with above-the-knee prostheses, and 15 bilateral prosthesis users. The recruitment and data collection period of the study is expected to be completed by March 2027. Dissemination of results is expected to be completed by December 2027.

It is expected that the side-by-side adaptability of the investigational prosthetic foot will improve community functions such as gait over uneven ground and cross slopes, weight shift during two-legged standing, side-stepping, turning, and precise positioning of the foot at initial stance. Evidence from this study is intended to help clinicians weigh options regarding the use of a prosthetic foot with a passive adaptable ankle in the frontal plane for their patients.

## Discussion

### Expected Findings

It is expected that the side-to-side adaptability of the META Arc prosthetic foot will help people with above-knee amputations, people with bilateral amputations, and people with lower levels of mobility manage their everyday activities better. It is expected that the results of this study will demonstrate that people with lower levels of mobility can complete non–straight gait tasks such as turning better and will participate in more challenging activities every day.

It is hypothesized that participants with bilateral amputations will report greater satisfaction, mobility, and comfort when using a prosthetic foot with frontal plane adaptability (unlocked condition) than when wearing a prosthetic foot without frontal plane adaptability (locked), as measured by the PLUS-M. It is also expected that participants will demonstrate improved performance during the 3XF8W using a prosthetic foot with frontal plane adaptability compared to a foot without frontal plane adaptability.

A cutoff for the TUG in determining fall risk of ≥8.17 seconds has been previously determined by Sawers and Hafner [16]. However, it is not clear what part of the TUG is causing the increased risk. By completing component analysis, this study will determine what part of the TUG is causing times above this fall risk threshold.

A previous study of the META Arc foot showed that optimal stiffness for walking on flat surfaces is not the same as for turning [17]. Preliminary findings have shown that there are differences in stride length and swing time when comparing turning with the prosthetic foot on the inside or the outside of the turn. This may have some implications in the development of gait training and fall prevention strategies.

During logbook and interview analysis, it is expected that participants will report their perceived changes in person-specific mobility during activities that require frontal plane adaptability. The logbook and interviews will also provide feedback on the investigational foot regarding what aspects the participants did or did not like. This information will be very useful for making improvements for the next version if needed. Preliminary logbook analysis has shown that participants have engaged in walking on uneven terrain and participated in activities such as walking the dog, hiking, and shopping with benefits while wearing the investigational foot.

The study populations are particularly relevant to veterans and service members with amputations resulting from combat-related trauma or disease. Prosthesis users should be challenged to move sideways, move backward, and turn. Biomechanical components are often conflated with typical summary scores, which are typically based on the time it takes to complete a task. By conducting component analysis, mobility challenges, prosthetic design, and training can be addressed to better fit the needs of the users.

There are some limitations to the protocol. The participants have a 2-week accommodation period for each phase of the A1-B1-B2-A2 crossover design. There is no structured training program. Although the order of locked and unlocked use of the study foot will be varied between individuals, participants may continue to become more accustomed to using the foot into the next period, with the possibility of bias in the results.

### Conclusion

The study will use a design that allows participants to get used to using two forms of the investigational foot: the locked and unlocked versions. This unique study design feature allows for comparing the investigational foot to a standardized control foot in a randomized order. Accommodation for participants in understudied groups may facilitate recruitment. Findings from this study are expected to generate new knowledge on the functional benefits of frontal plane adaptability, informing prosthetic design and clinical practice.
